# 1 SUMMARY

## 1.1 Summary of trial design

### 1.1.1 Design

This is a randomised, three-centre, factorial design to assess a prophylactic HIV vaccine with the HIVIS DNA prime administered ID by the Zetajet® device with or without the Derma Vax™ electroporation device at a dose of 0.6mg in a concentration of 3mg/ml or in a concentration of 6mg/ml, followed by IM MVA-CMDR 10^8pfu per ml either alone or given at the same time as IM 100 µg CN54 rgp140 adjuvanted with 5µg GLA-AF.

Approximately 18 participants will be allocated to receive placebo. Clinical staff will not know who received placebo, but they cannot be blinded to the group, and will know whether the participant is allocated to electroporation, and receives one or two injections at each timepoint. Laboratory staff will be blind to the group and the allocation of placebo.

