Participants will be contacted by phone, home visit or clinical contact at the first day following immunization for a brief adverse reaction interview. Additionally, participants will complete diaries over events for the evening of the vaccination day and the 7 days following each vaccination. A diary card (**see Appendix 6**) will be provided after each immunization, with instructions and a full verbal explanation for volunteers to record local and systemic adverse events following immunization, as well as any medication taken. A folder with a diary card, thermometer and a ruler will be issued to each volunteer. The clinical team will provide contact information as well as a telephone number to call 24 hours, in order to assure contact with the study personnel if needed. Furthermore the study clinic will contact participants by phone within 48 hours after each immunization to assure their well being.

All participants will be asked to contact the study site in the case of adverse events of suspected grade 2 or more for evaluation. A decision to offer the participants a visit to the clinic should be made and documented in the source documents. All volunteers with suspected grade 3 or more should be seen by the study physician and documented in the source documents.

Safety follow-up visits are scheduled at week 2 and week 4 after each immunization visit. Diary cards will be reviewed and discussed at the scheduled 2 weeks follow-up visit after each vaccination. Diary entries will be transcribed after revision and discussion with the participant during the follow up visits after each vaccination into a Vaccine/Reaction Form.

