#### **7.5.5 Solicited local and systemic clinical and laboratory adverse events**

Various local and systemic adverse events are known to be associated with licensed vaccines, and are referred to as '**solicited adverse events**'. These include disturbances in routine laboratory parameters, and are described in **Table 2** below.

Information on solicited adverse events will be collected at the clinics before and 30 minutes after each immunisation through direct questions asked during a structured face to face interview and through examination. This information will be recorded directly into the CRF. Participants will also be asked to complete a diary card (**Appendix 6**) recording solicited adverse events that start within 7 days of each immunisation, regardless of the route of immunisation they receive. Diary cards will be reviewed and discussed later at the scheduled 2 weeks follow-up visit after each immunisation, when the clinician will also enter solicited adverse event data onto the CRF. Diary card entries (e.g. severity grade of symptoms) might

be revised after discussion between the participant and the clinician. Any alterations should be dated and initialled by the study clinician directly onto the diary card. Where there is a discrepancy for the grade assigned on the same day as the visit, it is assumed that the grade assigned by the clinician is more accurate. Any discrepant report between the diary card and the CRF entry will be foot noted in the study report and analysis tables

All participants will be asked to contact the study site in the case of adverse events of suspected grade 2 or more for evaluation within the 7 days post immunisation period. A decision to offer the volunteer a visit to the clinic should be made and documented in the source documents. All participants with suspected grade 3 or more events should be seen by the study physician for further evaluations and confirmation of the reported grade.

In addition, systemic laboratory adverse events will be collected through routine laboratory testing according to the schedule (**Appendix 2**). These will be recorded on the standard laboratory reports and may be transcribed into the CRF or a copy of the laboratory report attached to the CRF.

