### 9.5.3 Safety variables

The original verbatim terms used by the investigator to identify AEs in the CRFs will be coded using an appropriate medical coding scheme (MedDRA). In all summaries, if a participant reports the same system organ class or preferred term more than once then the worst severity and worst relationship to trial vaccine will be taken. Discrepancies between diary card and CRF reports will be queried and resolved. It is assumed that the grade assigned by the clinician is more accurate, and this will be the grade reported in the tables. If the diary card grade is worse, this will be foot-noted.

All safety end-points will be graded by the Clinical Investigators and reviewed by the Trial Management Group. In the unlikely event that the TMG cannot reach consensus about grade and relationship to study product, an expert Endpoint Panel will be assembled.

Safety outcomes will be reported overall with proportion and 95% confidence interval, and by group and time-point, and by relationship to study product.

For the primary analysis of safety endpoints (as defined in **section 9.2.1**), results will be expressed as a proportion with confidence interval, and groups compared using Fisher's exact test.

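### Sections 7.5.5 and 9.5.3 give different rules on whose grade counts for solicited clinical events, and the wider rule lets staff who know the group set the tabulated grade for days they may not have examined the participant

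*Protocol*

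**What the plan says.** Participants grade their own reactions after each dose. Section 6.2 states that "participants will complete diaries over events for the evening of the vaccination day and the 7 days following each vaccination". Section 7.5.5 then has the cards checked at a clinic visit: "Diary cards will be reviewed and discussed later at the scheduled 2 weeks follow-up visit after each immunisation". At that visit the entries, severity grades included, may "be revised after discussion between the participant and the clinician", with changes dated and initialled on the card.

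On precedence, 7.5.5 presumes the clinician's grade to be more accurate under one condition: "Where there is a discrepancy for the grade assigned on the same day as the visit". It adds that any disagreement between card and CRF is to be footnoted in the report and analysis tables.

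Section 9.5.3, which governs the tables, sets no such condition: "It is assumed that the grade assigned by the clinician is more accurate, and this will be the grade reported in the tables". Its footnote rule is one-directional: "If the diary card grade is worse, this will be foot-noted".

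On blinding, section 1.1.1 says of clinical staff that "they cannot be blinded to the group, and will know whether the participant is allocated to electroporation", and that they also know whether one or two injections are given. They remain blind to vaccine versus placebo (sections 1.1.1 and 5.3).

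Section 9.2.1.2 defines the primary safety endpoint as a solicited event of grade 3 or worse, local, systemic or laboratory, or any event that leads to stopping immunisation. Section 9.5.3 compares groups by Fisher's exact test.

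**The concern.** An analyst cannot follow both sections. Under 7.5.5 a diary grade 3 on day 3, with no visit that day, carries no presumption in favour of a later clinician's grade. Under 9.5.3 the clinician's lower grade is tabulated and the diary grade becomes a footnote. The same participant can therefore be an event under one section and a non-event under the other.

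This matters because the endpoint depends on a single cut-point, and the person who may move a grade across it knows which regimens are being compared: electroporation or not, one or two DNA injections, protein added to the boost or not. In the Appendix 8 toxicity table, grade 3 for injection-site pain, chills, malaise, headache, muscle pain and joint pain rests on the participant being unable to carry on normal activities. A clinician who was not present that day has little independent evidence of this beyond the card and the conversation.

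**Working it through.** **1. The two rules side by side**

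| | Section 7.5.5 | Section 9.5.3 |
|---|---|---|
| Clinician's grade presumed better | Only for a grade assigned on a visit day | Whenever card and CRF disagree |
| Footnoted | Any discrepancy | Only a worse diary grade |
| Revision after discussion | Allowed, dated and initialled on the card | Not described; discrepancies queried and resolved |

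**2. Do diary days and the review day overlap?**

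- Diary: day 0 (evening) to day 7 (section 6.2).
- Two-week visit: day 14 ± 3, so days 11 to 17 (section 7.1.2).
- Shared days: none. Gap from entry to review: 11 − 7 = 4 days at the shortest, 17 − 0 = 17 days at the longest.
- Section 7.1.2 also gives ± 7 days for the visit two weeks after the second MVA dose: days 7 to 21. There only day 7 could coincide, and the gap runs from 0 to 21 days.

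At the usual review, then, the same-day presumption of 7.5.5 reaches no diary entry, while 9.5.3 reaches all of them. The 7.5.5 presumption can still apply on the immunisation day itself or at an unscheduled visit within the diary week.

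**3. Weight of one regraded event** (group sizes from section 9.3)

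- DNA comparison: 1/60 = 1.7 percentage points.
- Boost comparison: 1/90 = 1.1 percentage points.

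**4. Illustration of what one-sided regrading could do**

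The protocol gives no expected rate or power for the safety endpoint, so the rates and downgrading shares below are assumptions. The alpha levels are those that section 9.3 sets for the two randomisations. Method: exact power of the two-sided Fisher test by binomial enumeration. The rate seen in the higher arm is the true rate × (1 − share downgraded); for 25%, that is 25%, 18.75% and 12.5%.

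| True rates | n per group, alpha | None downgraded | 25% of higher arm's events downgraded | 50% downgraded |
|---|---|---|---|---|
| 5% v 25% | 60, 0.025 | 77% | 45% | 12% |
| 5% v 20% | 60, 0.025 | 52% | 24% | 5% |
| 10% v 30% | 60, 0.025 | 63% | 27% | 5% |
| 5% v 25% | 90, 0.05 | 97% | 79% | 35% |

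The opposite case, a spurious difference, is weaker. If both groups truly had 6/60 and half were downgraded in one group only, the result would be 3/60 v 6/60 (5% v 10%), with Fisher p = 0.49. The estimate is distorted, but the planned test gives no false signal.

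**The case against.** Several points on the other side stand.

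- **The diary is not group-blind either.** Participants are blinded only to vaccine versus placebo (section 5.3). They feel the electroporation, which section 2.4.6 describes as an unpleasant muscle contraction, and they know how many injections they had. A reader might infer that the original diary entry is the unbiased measure and ought to be primary. The documents do not support that: its advantage is that it was made at the time, not that its author is unaware of the group.
- **Section 7.5.5 never makes the unrevised card the primary grade.** It allows revision after discussion with the participant, and section 6.2 has entries transcribed after that step. The conflict is about whose grade prevails and on which days, not about whether revision is permitted.
- **Early safeguards exist at the cut-point.** Section 6.2 provides contact on the first day after each dose, a call within 48 hours and a 24-hour telephone number. Both sections have suspected grade 3 events seen by a physician, and 7.5.5 adds confirmation of the grade. Some grade 3 entries will therefore have been examined in time. This depends on the event being reported, and 9.5.3 applies whether or not an examination took place.
- **Grades are reviewed.** Discrepancies are queried, and the Trial Management Group reviews endpoints, with an Endpoint Panel if it cannot agree. The group includes site investigators (section 15.2) and is not described as blind to group, so this adds scrutiny but not a group-blind grade.
- **Only part of the endpoint is exposed.** Laboratory grades and discontinuations do not pass through the diary rule.

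It can also be argued that 9.5.3 is merely shorthand for 7.5.5. If so, the shorthand omits the condition that limits the rule, in the section that governs the tables.

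**Conclusion.** The contradiction is real, on precedence and on footnotes, and it can change the count of grade 3 solicited clinical events in the primary safety comparison. The dropped same-day condition is not a detail: at the usual review it separates no diary entries from all of them.

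The documents do not support the further inference that the safety comparison is biased. The direction and size of any effect cannot be derived from the protocol. The power figures show only that one-sided downgrading, if it occurred, could hide a sizeable difference, and they rest wholly on assumed rates and shares. Nor do the documents suggest that staff can favour vaccine over placebo, since they do not know that allocation. The point deserves correction because the ambiguity is avoidable and the remedy costs little.

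**What to change.** 1. Replace the two passages with one precedence rule, stated identically in 7.5.5 and 9.5.3: the clinician's grade takes precedence for days on which the participant was examined. State which grade is the primary one for the remaining diary days.
2. Adopt one footnote rule in both sections.
3. Keep both the original diary grade and the revised grade in the database. Alterations are already dated and initialled on the card, so the source exists.
4. Report the grade 3 or above solicited endpoint by group under both grades, one as primary and the other as a sensitivity analysis named before the main analysis, in place of a footnote. Which of the two is primary is a judgement for the trial team; what matters is that it is fixed in advance and that both results are shown.

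The cost is one extra data field and one extra table. No visit or procedure is added. If the two tables agree, regrading did not drive the comparison; if they differ, the reader can see by how much and in which group.

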## 10 DATA MANAGEMENT

Data management, analysis and reporting of all trial data will be prepared according to detailed Data Management and Statistical Analysis Plans. NIMR will be the Data Coordinating Centre (DCC) with primary responsibility for data coordination, supported by the MRC CTU in London.

Any data analyses carried out independently by investigators should be submitted to NIMR before publication or presentation and be reviewed by the TaMoVac Steering Committee (see **sections 15.3 and 16**).

### 10.1 Data management at the Clinical Centre

Staff at the clinical centre will be responsible for:

- Entering relevant information in the clinical notes and holding a record for each participant which includes the CRFs with any changes made signed and dated
- The accurate completion of the CRFs
- Collection of the diary cards from participants
- Notification of SAEs within 2 working days of becoming aware of the event as indicated in Section 8.2
- Notification of pregnancy within 2 working days of becoming aware of the pregnancy as indicated in Section 8.2

Data will be recorded directly onto the clinical notes and the CRFs in the most logical order, which may not necessarily always be the clinical notes followed by the CRF. For example the recording of the solicited adverse events will be done directly onto the CRF with additional details provided in the clinical notes if required. Similarly if the screening CRF does not reveal any medical history of relevance then this negative finding will not be duplicated in the clinical notes. Additional detail will be expected should there be a clinical abnormality relevant to eligibility. The dates of visits including immunisation, dates and results of pregnancy tests, and details of clinical management (description of adverse events and concomitant medication) will be detailed in the clinical notes. Other source data are described in **Table 5**. Data entry from CRFs will be performed at the sites by data entry clerks who are under supervision of a site data manager. All data will be double entered into a computerized database. An internal data monitoring with inconsistency and logic checks will run after double data entry. The resolution of queries and clearance of inconsistent data will be performed by the site data manager, and may require communication with the clinical team. Consistency checks and range checks will be performed at the data entry level on a daily basis.

**Table 5: The following table identifies the source documents:**

| Type of data                                                                            | Source document                                            |
|------------------------------------------------------------------------------------------------|-------------------------------------------------------------------|
| Informed consent                                                                               | Signed informed consent form                                      |
| Medical history                                                                                | Clinical notes, screening CRF and Previous Condition CRF Forms    |
| Physical examination, including height and weight                                              | Clinical notes and Physical Examination CRF Form, visit checklist |
| Demographics                                                                                   | Registration sheet and Screening CRF Forms                        |
| Laboratory data                                                                                | Laboratory reports                                                |
| Date/time of routine bloods; urinalysis dipstick and urine pregnancy test sampling and results | Clinical notes or visit checklists and Laboratory CRF Forms       |
| Date/time/result of solicited AEs including vital signs measurements post immunisation         | Clinical notes or visit checklists and Vaccine/Reaction CRF Form  |
| Date/time of immunisations                                                                     | Clinical notes or visit checklists and Vaccine/Reaction CRF Form  |
| Date/time of immunogenicity sampling                                                           | Clinical notes or visit checklists                                |
| Immunogenicity results                                                                         | Core Immunogenicity Laboratory File                               |
| IMP accountability                                                                             | Pharmacy File                                                     |
| Adverse events                                                                                 | Clinical notes and Adverse Events CRF Form                        |
| Concomitant medication                                                                         | Clinical notes and Concomitant Medication CRF Form                |
| Protocol deviations                                                                            | Clinical notes and Protocol Deviation CRF Form                    |
| Participant reported solicited AEs and concomitant medication                                  | Diary cards                                                       |

CRFs will be designed by Data Coordinating Center and provided to the site.

All data will be entered legibly in blue or black ink with a ball-point pen. If an error is made, the error will be crossed through with a single line in such a way that the original entry can still be read. The correct entry will then be clearly inserted and the alterations will be initialed and dated by the person making the alteration. Overwriting or use of correction fluid will not be permitted.

To preserve confidentiality, the CRFs will not bear the participant's name. The participant's date of birth and trial number (which will have been given at screening **section 4.4**) will be used for identification.

Laboratory reports must be signed by a member of the clinical trial team. In the event of an abnormality, an indication should be given whether or not action was taken, the date of review and the signature of the clinician reviewing the result.

CRFs and clinical notes should be kept in a secure location for 2 years after the last approval of a marketing application or until 2 years have elapsed since formal discontinuation of product development, and at least 15 years after the clinical trial has ended.

## **10.2 Data management in the immunology laboratories**

Standardized operating procedures will be followed in all laboratories to ensure the quality of data. Data will be stored in both hard copies and electronically in an agreed format. Standard operating procedures will be followed in all laboratories to ensure the quality of the data. Data will be stored electronically in an agreed format and datafiles transferred to the Trial Statistician for the main analysis.

## **10.3 Data management at the Central Data Management Centre**

The Data Coordinating Center (DCC) is located at NIMR, Dar es Salaam under the supervision of [name]. Mentorship will be provided by the MRC CTU under the supervision of [name]. NIMR will be responsible for the development and support of the trial database at each centre, and for the combined database held centrally at NIMR on behalf of the investigators. Guidance will be provided from the MRC CTU.

Central checks of the combined database will focus on the parameters required by the Trial Statistician for the analyses. Queries will be raised with the site senior data managers. Copies including documentation detailing all the queries and changes will be stored in a study specific binder at the DCC.

# 11 TRIAL MONITORING

## 11.1 Continuous and Internal Study Monitoring

Continuous study monitoring will be performed by the site teams, the Medical Experts and protocol co-Chairs and the Trial Management Group (TMG) who will closely monitor and review the study progress, adverse events reports, reactogenicity reports, protocol deviations, lab data and any other data available from the database. Internal study monitoring will be performed continuously at the study site by assigned internal monitors and the CRC. In addition regular internal monitoring visits will be performed by the Sponsor's Medical Expert. . This will include review of the study binders, source documents and case report forms, the study clinics and pharmacies, trial procedures and the need for training. Internal laboratory monitoring at the study laboratories will be done by [name] from the SMI.

## 11.2 TMG and safety calls during the study

Telephone conference calls will be held every 2-4 weeks and upon request/need. Calls will be organized by the UK MRC Clinical Trials Unit. TMG members will meet through these calls to up-date on the study progress, discuss adverse events, reactogenicity and protocol deviations and assist the site TMT in case management and resolutions. Prepared data management reports will be heard and reviewed. Laboratory and organisational issues will be discussed. Conference call agendas, minutes and follow-ups will be generated and distributed.

